**2.2.4 Phase I Studies**

The Phase I program with BMS 247550 has tested two different dose escalation schedules of administration: *CA163-001*: Day 1 of a 21-day cycle (q3 weeks) and *CA163-002*: Day 1, 8, 15 of a 28-day cycle (q week). The weekly schedule was chosen for this Phase II study based on evidence of profound neurotoxicity at the every 3 week schedule. (Correspondence from NCI to Epothilone Principal Investigators following NCI Phase I meeting 10/01) and results of the Phase I trial (CA 163-002).

##### Study CA163-001

Thirty-one patients have been enrolled in the CA163-001 study at 7.5, 15, 30, 50, 57, and 65 mg/m2. Enrollment was completed in August 2000 and 16 patients continue to receive subsequent cycles of BMS 247550 at doses of 40 (1 patient dose reduced), 50 (14 patients) and 57 (1 patient) mg/m2. Dose limiting toxicities observed at 65 mg/m2 included neuropathy, myalgia, arthralgia and neutropenia. One case of pneumonia leading to fatal pneumococcal sepsis occurred at the 50 mg/m2 dose level. Other observed toxicities (n=14) considered related to BMS 247550 were fatigue (43%), myalgia (29%), arthralgia (21%), alopecia (21%), nausea (21%), constipation (14%), vomiting (14%), and sensory neuropathy (14%). In addition to tingling and numbness, the neuropathy has been described to include pain in the extremities in some patients. Confirmed objective responses have been observed in one patient with melanoma and in taxane-pretreated patients, including one each with non-small cell lung cancer, with peritoneal (ovarian) cancer and with adenocarcinoma of unknown primary. After accrual to the dose escalation phase of the trial, 10 additional patients were accrued at a dose of 50 mg/m2. One patient in this group has required dose reduction for febrile neutropenia. Based on this Phase I experience, 50 mg/m2 given every three weeks has been selected as the Phase II dose. Routine premedication was started in all new patients after one occurrence of a hypersensitivity reaction (HSR) in this study at the 30 mg/m2 dose level; since introduction of premedication, no further significant hypersensitivity reactions occurred.

##### Study CA163-002

In an ongoing Phase I study (CA163-002, [name], Institut Jules Bordet, Brussels, Belgium), which started end of December 1999, BMS 247550 is given as a continuous weekly intravenous 30 minute infusion to patients with solid tumors. As of mid-July 2000 all new patients in this study also receive a single oral dose (cycle -1) of BMS 247550 on Day -6 before cycle 1. Plasma sampling is performed both during cycle -1 and cycle 1 to evaluate the pharmacokinetics and pharmacodynamics of BMS 247550 and the absolute oral bioavailability of BMS 247550. Routine premedication was started in all new patients after the second occurrence of a hypersensitivity reaction (HSR) in this study.

As of the end of August 2000, 17 patients have been treated on this dose-finding study. Three patients have been entered at the current dose level of 20 mg/m2. Together they have received 12 weekly administrations of BMS 247550 (3 of which were given orally). There have been no DLTs observed so far and after the introduction of standard premedication, no further HSRs occurred. The drug related toxicities reported so far are mild to moderate myalgia/arthralgia, asthenia, diarrhea, sensory neurotoxicity, anorexia and alopecia. One patient experienced hypotension CTC Grade 1 and bradycardia CTC Grade 2 after the 5th infusion of 10 mg/m² intravenous BMS 247550. These events were possibly related to the drug.

**2.2.5 Potential For Hypersensitivity Reactions Related To Polyoxyethylated Castor Oil (CremophorEL)**

Based on the presence of polyoxyethylated castor oil in the formulation of BMS 247550, the potential for hypersensitivity reactions exists with intravenous administration of this compound. In clinical trials of paclitaxel, anaphylaxis and severe hypersensitivity reactions (dyspnea requiring bronchodilators, hypotension requiring treatment, angioedema, and generalized urticaria) have occurred in 2% of patients (56). Three of the first twenty patients treated with BMS 247550 have experienced a hypersensitivity reaction. Since instituting routine premedication, none of the remaining patients have experienced a significant hypersensitivity reaction. Hence, routine premedication will be used in this trial (see Section 4.1.1 for prophylaxis for hypersensitivity reactions).

**2.3 Rationale**

The Phase I program with BMS 247550 has tested two different dose escalation schedules of administration: Day 1 of a 21-day cycle (q3 weeks) and Day 1, 8, 15 of a 28-day cycle (q week). The weekly schedule was chosen for this Phase II study based on evidence of profound neurotoxicity at the every 3 week schedule. (Correspondence from NCI to Epothilone Principal Investigators following NCI Phase I meeting 10/01) and results of the Phase I trial (CA 163-002).

**3. PATIENT SELECTION**

**3.1 Eligibility Criteria**

3.1.1 Patients must have histologically or cytologically confirmedmalignant melanoma stage IV.

3.1.2 Patients must have measurable disease, defined as at least one lesion that can be accurately measured in at least one dimension (longest diameter to be recorded) as >20 mm with conventional techniques or as >10 mm with spiral CT scan. See section 9.1.1 for the evaluation of measurable disease.

3.1.3 Prior therapy

Two subgroups of patients will be treated:

**Subgroup A: Chemotherapy naïve**

These patients may not have received any prior chemotherapy

**Subgroup B: DTIC pretreated**

These patients may have received a maximum of two prior lines of chemotherapy, and must have received DTIC or temozolomide.

Prior vaccine therapy, immunotherapy (e.g. IL-2, interferon) and radiotherapy are permitted in both subgroups. Patients treated with limb-perfusion are eligible and will be assigned to Subgroup B.

No minimum period since last therapy is defined, but patients must have adequate organ toxicity as defined in 3.1.7, and preexisting non-hematological dysfunction <grade 2.

3.1.4 Age 18 years.

Because no dosing or adverse event data are currently available on the use BMS 247550 in patients <18 years of age, children are excluded from this study but will be eligible for future pediatric single-agent trials, if applicable.

3.1.5 Life expectancy 3 months.

3.1.6 ECOG performance status 0-2 / Karnofsky 60% (see Appendix B).

3.1.7 Patients must have normal organ and marrow function as defined below:

- absolute neutrophil count 1.5 x 109/l
- platelets 100 x 109/l
- total bilirubin within normal institutional limits
- AST (SGOT) / ALT (SGPT) 2.5 x upper limit of normal
- creatinine 1.5 x upper limit of normal

3.1.8 Patients with known brain metastases may be included in this study if they fulfill all of the following criteria:

- the lesions have remained radiologically stable for at least six weeks after completion whole brain irradiation, and remain stable at the time of study entry
- there is no mass effect present radiologically
- the patient is no longer receiving steroids to control symptoms of brain metastases

3.1.9 The effects of BMS 247550 on the developing human fetus at the recommended therapeutic dose are unknown. Women of child-bearing potential and men must therefore agree to use adequate contraception (hormonal or barrier method of birth control) prior to study entry and for the duration of study participation. Should a woman become pregnant or suspect she is pregnant while participating in this study, she should inform her treating physician immediately.

3.1.10 Ability to understand and the willingness to sign a written informed consent document.

**3.2 Exclusion Criteria**

3.2.1 Patients may not be receiving any other investigational agents.

3.2.2 History of severe allergic reactions (Grade III or IV or Grade II not responsive to steroids) attributed to taxanes or medications containing CremophorEL.

3.2.3 Patients with preexisting peripheral neuropathy of grade 2-4 are excluded from this study

3.2.4 Uncontrolled intercurrent illness including, but not limited to, ongoing or active infection, symptomatic congestive heart failure, unstable angina pectoris, cardiac arrhythmia, or psychiatric illness that would limit compliance with study requirements.

3.2.5 Pregnant women are excluded from this study because the teratogenic or abortifacient effects of BMS 247550 are unknown. Because there is an unknown but potential risk for adverse events in nursing infants secondary to treatment of the mother with BMS 247550, breastfeeding should be discontinued if the mother is treated with BMS 247550.

- - 1. Because patients with immune deficiency are at increased risk of lethal infections when treated with marrow-suppressive therapy, HIV-positive patients receiving combination anti-retroviral therapy are excluded from the study because of possible pharmacokinetic interactions with BMS 247550. Appropriate studies will be undertaken in patients receiving combination anti-retroviral therapy when indicated.

**3.3 Inclusion of Women and Minorities**

*Both men and women and members of all ethnic groups are eligible for this trial, although accrual of non-white patients is expected to be low as melanoma is rare in non-white ethnic groups. Based on accrual in previous melanoma studies at NYU and Sydney, the proposed study population is illustrated in the table below:*

|  | **Race/Ethnicity** | | | | | |
| --- | --- | --- | --- | --- | --- | --- |
| **Gender** | White, not of Hispanic Origin | Black, not of Hispanic Origin | Hispanic | Asian or Pacific Islander | Unknown | Total |
| Male | 60% | 0 | 0 | 0 | 0 | 60% |
| Female | 40% | 0 | 0 | 0 | 0 | 40% |
| Total | 100% | 0 | 0 | 0 | 0 | 100% |

**4. TREATMENT PLAN**

**4.1 Agent Administration**

Treatment will be administered on an outpatient basis. Expected adverse events and appropriate dose modifications for BMS 247550 are described in Section 5. No investigational or commercial agents or therapies other than those described below may be administered with the intent to treat the patient’s malignancy. **Note**: St. John’s Wart significantly induces cytochrome p450 3A4 and may affect the metabolism of BMS 247550. Administration is not permitted on this study.

###### 4.1.1 Premedication

Since BMS 247550 is formulated in polyoxyethylated castor oil (CremophorEL), hypersensitivity reactions may occur. Therefore, patients should be monitored closely for any signs or symptoms of hypersensitivity and emergency equipment must be available to treat possible anaphylactic/ anaphylactoid reactions as outlined in Section 4.2.2.

**All patients will receive the following premedication to minimize nausea, vomiting and hypersensitivity reactions:**

**Diphenhydramine** 50mg IV (or equivalent,) 1 hour prior to BMS 247550

**Ranitidine** 50mg IV **(or equivalent)**, 1 hour prior to BMS 247550

**Ondansetron** 8mg IV/oral **(or equivalent)**, immediately prior to BMS 247550

**Dexamethasone** 20mg IV, immediately prior to BMS 247550

###### 4.1.2 BMS 247550

All patients will receive:

**BMS 247550 20 mg/m2, 1 hour infusion, weekly x3 followed by 1 week break**

This dose may subsequently be reduced for individual patients, depending on toxicity (Section 5.2). In calculating surface areas, actual heights and weights should be used; that is, there should be no adjustment to “ideal” weight. The total dose delivered should be rounded to the nearest mg.

See Section 6.1.5 for details on preparation of BMS 247550 for intravenous administration.

An infusion pump must be used to deliver BMS 247550 over one hour during cycle 1 in which pharmacokinetics is collected. After confirming that the required volume has been administered, solution remaining in the line and container should be disposed of per institution policies for cytotoxic disposal. The patient’s blood pressure and heart rate should be measured at baseline and every 15 minutes during the infusion of BMS 247550, and a nurse must be present in the immediate treatment area throughout the infusion. A physician must be in close proximity to the patient treatment area.

**4.2 Supportive Care Guidelines**

**4.2.1 Growth Factors**

Hematological growth factors will not be used prophylactically in this study, but may be used at the discretion of the investigator in the event of severe hematological toxicity.

##### 4.2.2 Hypersensitivity Reactions

**Treatment**

In case of hypersensitivity reactions, the Investigator should institute treatment measures deemed medically appropriate. Based on prior experience with paclitaxel, the following treatment recommendations may be applicable:

CTC Grade 1 Allergic Reaction/Hypersensitivity (transient rash, drug fever <38C):

- Supervise at the bedside

CTC Grade 2 Allergic Reaction/Hypersensitivity (urticaria, drug fever 38C, and/or asymptomatic bronchospasm):

- Interrupt the infusion of BMS 247550
- Give IV antihistamines (diphenhydramine 25-50mg, and ranitidine or famotidine)

**Note**: Cimetidine inhibits cytochrome p450 3A4 and may effect the metabolism of BMS 247550, resulting in increased blood drug concentrations. This H2 blocker is therefore not permitted on this trial.

- After recovery of symptoms, resume the infusion at a slower rate and if no further symptoms appear, complete the administration of the dose. (Note: It is recommended that the infusion of BMS 247550 be completed within 3 hours of the final dilution. See Section 6.1.6).
- If symptoms recur, stop the infusion and proceed with interventions listed in CTC Grade 3 or 4 below.

CTC Grade 3 or 4 Allergic Reaction/Hypersensitivity (symptomatic bronchospasm requiring parenteral medication(s) with or without urticaria; allergy-related edema/angioedema; anaphylaxis):

- Stop the infusion of BMS 247550.
- Administer additional doses of H1 and H2 blockers intravenously.
- Administer epinephrine, and nebulized bronchodilators as medically indicated.
- Consider IV steroids which may prevent recurrent or ongoing reactions.
- If grade 4, report adverse event (see Section 10.2)
- Patient off study, or rechallenge with premedication (see below) after 24 hours, based upon the judgment of the Investigator and the Protocol Chair

**Rechallenge**

Suggested regimen for rechallenge of BMS 247550 after a Grade 3 or 4 hypersensitivity reaction despite recommended premedication:

- **Dexamethasone** 20 mg PO at 12 and 6 hours before BMS 247550 infusion.
- **Diphenhydramine** 50mg IV 30minutes before BMS 247550.
- **Ranitidine** 50mg or **Famotidine** 20mg IV 30 minutes before BMS 247550.
- Begin BMS 247550 at **25% of the previous rate** for 1 hour;
- **Increase rate gradually** to complete the total infusion within 3 hours from the time the drug was diluted in Lactated Ringer’s Injection (LRI) (see Section 7.2.1).

**4.2.3 Contraception**

Women of childbearing potential and sexually active males are strongly advised to use an effective method of contraception.

**4.2.4 Other**

Other appropriate supportive care medications may be administered at the investigator’s discretion.

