Comparison of the human plasma exposure data (Cmax and AUC) from the ongoing first-in-human study (CA163-001) at the 50 mg/m2 dose level with the plasma exposures observed in single dose IV rat and dog toxicokinetic studies (51,52) is provided in the table below:

| Species | IV Dose  (mg/m2) | Cmax (ng/mL)a  [multiple of human exposure] | AUC(INF) (h.ng/mL)  [multiple of human exposure] |
| --- | --- | --- | --- |
| Rat  Male (N = 3)  Female (N = 3) | 60  60 | 6422 [7.6]  8384 [10.0] | 3864 [1.3]  8156 [2.7] |
| Dog (2M, 2F)b | 10 | 218 [0.3] | 258 [0.1] |
| Dog (2M, 2F)b | 100 | 5118 [6.1] | 6925 [2.3] |
| Human (N = 6) | 50 | 841 [1.0] | 3076 [1.0] |

a Dosing in animals was a 10-minute infusion while that in humans was a 1-h infusion.

b Combined across gender due to small sample size N = 2/gender.

AUC values of BMS 247550 at the lowest dose tested in rat toxicokinetic studies (60mg/m2, close to the STD10 of 74mg/m2) were higher by 1.33 and 2.9-fold in male and female rats, respectively, compared to the exposures in humans at a dose of 50mg/m2. At the well-tolerated dose of 10mg/m2 in dogs, the plasma AUC was about 11.9-fold lower as compared to the exposure in humans at 50mg/m2. However, at the lethal dose of 100mg/m2 in dogs, the plasma AUC values in dogs were higher by 2.3-fold compared to the plasma AUC observed in humans at 50mg/m2.

Metabolism in Humans and Potential for Metabolic Drug Interactions

Formal characterization of BMS 247550 metabolism in humans has not been completed. BMS 247550 undergoes oxidative metabolism when incubated with human liver microsomes *in vitro*. When BMS 247550 was incubated with human liver microsomes along with compounds specific for the inhibition of individual cytochrome P450 enzymes, almost complete inhibition was observed only with the CYP3A4 inhibitors (troleandomycin and ketoconazole) suggesting that BMS 247550 may be a substrate for CYP3A4 in humans.

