**5.2 Dosing Delays / Dose Modifications**

Prior to retreatment, patients must have recovered the following organ function:

- absolute neutrophil count 1.0 x 109/l
- platelets 100 x 109/l
- total bilirubin within normal institutional limits
- AST (SGOT) / ALT (SGPT) 2.5 x upper limit of normal
- creatinine 1.5 x upper limit of normal
- other Grade 0-1

Any patient experiencing the relevant toxicities (cited below in section 5.2) after one dose reduction will be removed from the protocol.

Patients should be dose reduced to 16 mg/m2 IV (20% dose reduction) over 1 hour in the event of any of the following:

- grade 4 neutropenia 5 days
- febrile neutropenia
- grade 4 thrombocytopenia
- grade 3 non-hematological toxicity
- 1 week delay for recovery from any toxicity

No patients should have his / her dose re-escalated following dose reduction.

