**Reported Adverse Events and Potential Risks:**

Allergic reactions (anaphylaxis)/hypersensitivity (including drug fever), leukopenia, neutropenia, granulocytopenia, sinus bradycardia, edema, hypotension, fatigue (lethargy, malaise, asthenia), fever, alopecia, dermatitis, flushing, pruritus, radiation recall reaction, rash/desquamation, anorexia, constipation, diarrhea, nausea, stomatitis, dysgeusia, vomiting, febrile neutropenia, infection, muscle weakness (not due to neuropathy), dizziness/lightheadedness, insomnia, motor neuropathy, tingling, numbness, speech impairment (dysphasia or aphasia), syncope, arthralgia, myalgia, neuropathic pain, phantom limb pain, post-infection neuralgia, painful neuropathies, pain in extremities, cough, dyspnea, hiccoughs, hypoxia, pneumonitis/pulmonary infiltrates, urinary retention.

Also reported on BMS-247550 trials but with the relationship to BMS-247550 still undetermined: decreased hemoglobin, thrombocytopenia, hyperglycemia, hyperkalemia, hypocalcemia, transaminitis, ataxia, cerebrovascular ischemia (1 case), seizures (1 case).

**Potential Drug Interactions:** BMS-247550 may have a minimal potential to alter the metabolic clearance of drugs that are

highly metabolized by CYP3A4. When BMS-247550 was incubated with human liver microsomes along with compounds

specific for the inhibition of individual cytochromeP450s, significant inhibition was observed only with the CYP3A4 inhibitors

(troleandomycin and ketoconazole) suggesting that BMS-247550 may be a substrate for CYP3A4 in humans.

**Incompatibilities:** Contact of the diluted product with polyvinyl chloride (PVC) equipment or devices that are plasticized

with di- (2-ethylhexyl)pthalate (DEHP) should be avoided to prevent leaching of DHEP into the infusion medium. In order

to minimize patient exposure to DEHP, which my be leached from PVC infusion bags or sets diluted BMS-247550

solutions should preferably be stored in bottles (glass, polypropylene) or plastic bags (polypropylene, polyolefin) and

administered through polyetheylene-lined administration sets or PVC sets plasticized with TOTM (trioctyl trimellitate). IV

sets and components typically used for the administration of paclitaxel have been found to be compatible with infusions of

BMS-247550.

The following infusion components have been qualified for use with BMS-247550**:**

- IV sets containing an in-line 0.22 micron filter
  1. Baxter Vented Paclitaxel Set (Catalog #2C7553)

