**NYU 00-57 STUDY CALENDAR**

Baseline evaluations are to be conducted no more than 1 week prior to administration of study agent. Scans and x-rays must be done no more than 4 weeks prior to the start of therapy. If the patient’s condition is deteriorating, laboratory evaluations should be repeated no more than 48 hours prior to initiation of the next cycle of therapy.

|  | **Pre-Study** | **Each cycle** | | **Every 2 cycles** | **Off Study** |
| --- | --- | --- | --- | --- | --- |
| **D1, D8, D15** | **Prior to next cycle (D22-27)** |
| BMS 247550 |  | X |  |  |  |
| **Informed consent** | X |  |  |  |  |
| **Demographics** | X |  |  |  |  |
| **Medical history** | X |  | X |  |  |
| **Physical exam** | X |  | X |  |  |
| **Vital signs** | X | X |  |  |  |
| **Height / Weight** | X | X |  |  |  |
| **Medications** | X |  | X |  |  |
| **Performance status** | X |  | X |  | X |
| **Hb, ANC, plts*** | X | X | X |  |  |
| **Serum chemistry**** | X |  | X |  |  |
| **EKG (as indicated)** | X |  |  |  |  |
| **B-HCG** | X |  |  |  |  |
| **Adverse Events** |  | X | X |  | X |
| **Tumor Measurements** |  |  |  | X |  |
| **Collection of PBPC’s (1 & 24h: cycles 1 &2)** | X | X |  |  |  |
| **Tumor Biopsy (1 & 24h cycles 1 &2)** | X | X |  |  | X |

* If a patient develops Grade 4 neutropenia, CBC’s will be checked 3 times per week until resolution.

** Electrolytes, calcium, magnesium, liver function tests and LDH.

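### Cimetidine and St. John's Wort are barred for CYP3A4 effects, but ketoconazole and troleandomycin are left to investigator discretion, and no medication review is scheduled on dosing days

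*Protocol*

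**What the plan says.** Three parts of the protocol restrict a medicine or a patient group because of a possible interaction with the study drug:

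- Section 4.1 does not permit St. John's Wort because it "significantly induces cytochrome p450 3A4 and may affect the metabolism of BMS 247550".
- Section 4.2.2 does not permit cimetidine. The reason given is: "Cimetidine inhibits cytochrome p450 3A4 and may effect the metabolism of BMS 247550, resulting in increased blood drug concentrations".
- Section 3.2 states that "HIV-positive patients receiving combination anti-retroviral therapy are excluded from the study because of possible pharmacokinetic interactions with BMS 247550".

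The in vitro data on what inhibits the drug's metabolism appear in Section 2.2 and again in Section 6.1. Under the Section 2.2 heading on metabolism in humans, human liver microsomes were incubated with enzyme-specific inhibitors and "almost complete inhibition was observed only with the CYP3A4 inhibitors (troleandomycin and ketoconazole"). Section 6.1, under potential drug interactions, says "significant inhibition was observed only with the CYP3A4 inhibitors" and names the same two agents. Both places conclude only that the drug may be a CYP3A4 substrate in humans.

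Section 4.2.4 is the general rule for other medicines: "Other appropriate supportive care medications may be administered at the" investigator's discretion.

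The medications row of the study calendar reads "Medications | X | | X": marked before the study and at D22-27, and blank under D1, D8 and D15.

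**The concern.** The reason given for barring cimetidine is that it inhibits CYP3A4 and may raise drug levels. That reason applies at least as directly to ketoconazole and troleandomycin, the only inhibitors for which the protocol reports data with this drug. Yet no eligibility, treatment or supportive-care section bars them or warns against giving them.

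The gap is not remote. Section 5.1 lists neutropenia as dose limiting, and mucositis and febrile neutropenia each at 5-20% of patients. It is my inference, not a protocol statement, that antifungals and macrolides are foreseeable supportive care here.

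If raised exposure caused a toxicity listed in Section 5.2, the dose would fall to 16 mg/m2. That step is permanent: "No patients should have his / her dose re-escalated following dose reduction". A further listed toxicity after one reduction means removal from the protocol. A patient could lose dose, or treatment altogether, because of an avoidable co-medication.

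**Working it through.** The plan states no figure to reproduce. The check compares its provisions, counts the days between reviews, and gives an exposure scale by assumption.

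**1. Does any other provision reach these inhibitors?**

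| Provision | Does it restrict ketoconazole or troleandomycin? |
| --- | --- |
| Section 4.1, other agents | No. It covers agents given with anticancer intent, plus St. John's Wort. |
| Section 4.2.2 | No. It names cimetidine only. |
| Section 3.2 | No. It covers combination anti-retroviral therapy in HIV-positive patients. |
| Section 4.2.4 | No. It leaves the choice to the investigator. |
| Section 6.1, potential drug interactions | No. It names both agents but gives no instruction. |
| Appendix D checklist | No. It has no medication item. |

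The reassurance in Section 2.2 that clinically important interactions are unlikely concerns the study drug's effect on other medicines metabolised by CYP3A4. It does not address other medicines raising study-drug exposure.

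**2. How long can an inhibitor go unreviewed?**

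Doses fall on D1, D8 and D15 of a 28-day cycle. Medications are reviewed before the study and at D22-27, so every D1 dose follows a scheduled review. The gap is at D8 and D15.

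- Started D2: doses given with it on board are D8 and D15, so 2 of 3. Delay to review is 22 − 2 = 20 to 27 − 2 = 25 days.
- Started D9: dose given with it on board is D15, so 1 of 3. Delay to review is 22 − 9 = 13 to 27 − 9 = 18 days.

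These are illustrations with the inhibitor started the day after a dose. A medicine still in use at D22-27 is recorded late, not lost.

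**3. What could the exposure change look like?**

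The documents give no in vivo figure, and Section 2.2 says formal human metabolism and interaction studies are not complete. As a scale only, take AUC = dose / clearance and assume a range of clearance falls:

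| Assumed fall in clearance | AUC multiplier | 20 mg/m2 gives the exposure of |
| --- | --- | --- |
| 20% | 1 / 0.80 = 1.25 | 20 × 1.25 = 25 mg/m2 |
| 33% (one third) | 1 / 0.67 ≈ 1.50 | 20 × 1.50 = 30 mg/m2 |
| 50% | 1 / 0.50 = 2.00 | 20 × 2.00 = 40 mg/m2 |

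At the smallest assumed fall, the reduced dose gives 16 × 1.25 = 20 mg/m2, so the single permitted reduction would be fully offset while the inhibitor continued.

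**The case against.** The strongest reply is that the protocol informs the prescriber and leaves a sensible choice. Section 4.2.4 allows only appropriate medicines, and Section 6.1 names both inhibitors under potential drug interactions. The human evidence goes no further than a possible substrate. The Investigator Brochure, not available here, may say more. The cimetidine note can also be read as targeted: premedication calls for ranitidine or an equivalent, which could lead a site to cimetidine, and nothing in the treatment plan leads a site to ketoconazole.

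Other points limit the size of the problem:

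- Adverse events and blood counts are checked on every dosing day, and Section 5.2 requires recovery before retreatment.
- The calendar is not exhaustive. It has no pre-study mark for tumor measurements, although Sections 9.1.3 and 9.2 require them at baseline.
- Between-patient variation in clearance is already large. In the Section 2.2 table, cycle 1 standard deviation over mean is 114/327 = 35%, 146/398 = 37% and 127/318 = 40% at 15, 30 and 50 mg/m2, and 20.7/230 = 9% at 7.4 mg/m2. The two smaller assumed falls lie within the 35-40% spread.
- The documents give no frequency of use for these inhibitors.

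These points stand as limits on the likely harm, but none closes the gap. The dosing-day checks detect toxicity after exposure; they neither ask about the inhibitor nor bar it. Naming an agent without an instruction leaves the decision with each site, which the protocol did not accept for cimetidine. Natural variation in clearance does not justify adding an avoidable shift to it.

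**Conclusion.** The point holds as an optional improvement to patient safety. The textual gap is certain: two agents are barred for CYP3A4 effects, the two inhibitors named in the protocol's own data are not, and medications are not scheduled for review on dosing days. In the D2 example, two of three doses in a cycle can be given before a review, with a delay of 20-25 days.

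The chain from inhibitor to toxicity to permanent reduction or removal is plausible but not quantified. It rests on in vitro data being relevant in patients, and the exposure figures rest on assumed clearance falls. The data do not rank ketoconazole or troleandomycin against cimetidine. No effect on the primary response-rate design is claimed.

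**What to change.** Make Section 4.2.4 subject to this rule: *Strong CYP3A4 inhibitors, including ketoconazole and troleandomycin, are not permitted during treatment, in the same way as cimetidine (Section 4.2.2).* The two named agents can be applied at once; because the protocol does not define a strong inhibitor, the sponsor should say which others it means.

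In the study calendar, mark medications on D1, D8 and D15, with the check made before each dose.

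The cost is one sentence and one calendar mark. Patients already attend on those days, so no visit is added. The downside is a slightly narrower choice of antifungals and macrolides.
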